##### Support

Supportive self-monitoring is a therapeutic intervention to improve mental health, based on tailored real-time feedback on the individuals’ own information collected during self-monitoring (56, 57). By self-monitoring mental health, it is expected that the user gains insights into his or her own mental health, learns to improve self-management skills and establishes healthy attitudes and behaviors. Tailored feedback based on the individuals’ information is provided in real time, to support and reinforce positive change in mental health, and to counteract negative developments. Figure 2 displays the supportive monitoring process.

**Figure 2 F2:**
[figure not shown]
Supported self-monitoring process.

*Self-Monitoring*: participants will be able to self-monitor mental health by visual inspection of the time course for each symptom (mood, anxiety, depression, stress, sleep, impairment). This will be achieved by displaying line plots of symptom scores on the *y*-axis, and time (in days) on the *x*-axis. Participants can select the last week or the total self-monitoring period as time frame. There will be an option to display the time course of multiple symptoms simultaneously by adding or removing symptoms from the menu.*Inference of Health Status*: weekly health reports will provide text-based feedback on the user’s personal health status and symptoms. The participants’ personalized weekly health status will be derived from the mean level for each symptom during the past week. Severity categories (low, moderate, high) will be computed by using established cut points, whenever available. For example, the established PHQ-4 cut points for symptom severity of depression (47) and anxiety (48) will be used. If no cut points are available, the scales will be divided into low, moderate, and high scores according to the tertiles of the frequency distribution. The health status will also be displayed in terms of deviations from the within person-mean. Thus, the participants’ deviation of his or her mean in terms of improvements or worsening of symptoms will be displayed. As a relatively stable mean requires several days of collected data, the latter feature will be available after 1 week of use. Users will be notified whenever a new weekly health report is available with a pop-up message and an icon next to the appropriate section.*Context information*: the influence of social contexts on mental health will be displayed to the user. The context-specific health status will be displayed on a text basis, allowing the users to compare the symptoms and health in each setting. For this purpose, each of seven symptoms will be grouped by its daily context/setting. Six different contexts will be available: 1. days with daily hassles, 2. days with daily uplifts, 3. days with physical activity, 4. days with social activity, 5. days spent alone, and 6. days in company (partner or friends, family, colleagues, others). Alternatively, users may group symptoms by five different locations (1. days at home, 2. days visiting friends or family, 3. days at work or school, 4. trips/outbound, and 5. other). Thus, the user can inspect his or her mental health problems within a total range of 210 possible combination, allowing for a rich and detailed inspection of symptoms by context.*Supportive Feedback*: personalized supportive feedback will be given, based on the data collected by the participant. Feedback will presented in the form of daily health tips which can be accessed from within the application or as Android system notification. The feedback will include tips for the self-management of mental health and mental health micro-interventions (e.g., behavioral activation, problem solving, coping strategies) based on psychoeducation and cognitive–behavioral therapy (CBT) for low mood, anxiety, depression, stress, substance abuse, and sleep problems (58–60). The feedback will be adapted to the severity of each symptom within the last week (low, moderate, high). In the case of low to moderate severity, tips for the self-management of mental health and mental health micro-interventions will be displayed. Participants with moderate symptom severity will also be directed toward available evidence-based self-help programs (61, 62). In the case of severe symptoms, participants will be encouraged to seek help from a professional mental health service and will be provided with corresponding contact information on these services (e.g., hotlines, addresses, and websites of professional organizations). For each mental health problem and degree of severity, at least 10 different feedback messages will be developed, resulting in a total of at least 180 feedback messages (10 messages × 6 mental health problems × 3 degrees of severity). Additionally, a total of 40 feedback messages will be developed for the presence of daily life risk factors for mental ill-health (low social activity, low physical activity, daily hassles, and functional impairment). Users will be able to dismiss feedback messages that they do not wish to be presented again or to select feedback messages that they wish to be reminded of. All content will be developed on the basis of evidence-based guidelines or treatment manuals for the respective mental health problems (63–67).

###### Content

*Psychoeducation*: Psychoeducation aiming at educating the user about the nature and treatment of mental health problems was found to be an effective and easy-to-implement intervention for depression, anxiety, and psychological distress (59). Psychoeducation can also help to reduce perceived stigmatization (68), and to enhance mental health literacy (69), beliefs in the efficacy of treatment options (70), and help-seeking behavior (71). As psychoeducation is most effective when the content is perceived as relevant for a persons’ problem, the intervention will offer relevant information on mental health problems adapted toward the user. This includes psychopathology from self-monitoring (mood, depression, anxiety, stress, sleep, and functional impairment) as well as risk and protective factors. The total educational content will be accessible *via* a knowledge base section within the smartphone application, and supportive feedback (daily health tips) will direct the users toward appropriate educational content, when indicated by self-monitoring information. Psychoeducation within the application will be limited to brief texts and visualizations, and links to further educational websites and resources will be provided for further reference.

*Cognitive–behavioral therapy*: Cognitive–behavioral therapy is one of the most extensively researched forms of psychological treatment. It aims toward improving mental health by challenging negative automatic thoughts and dysfunctional beliefs, and at changing behavioral patterns, including risk and protective factors related to mental health. CBT was found to be effective for a broad variety of mental health problems, including depression, anxiety, and stress (72–74). CBT is also a prevention technique which helps to prevent mental-health problems from maintaining, and is suitable for managing both clinical and subclinical mental health problems (75). CBT is also the recommended therapeutic principle for mHealth interventions, as it is feasible for self-administration by the user (76). In the context of mHealth, CBT has the advantage that its techniques are well suited for a text-based operationalization, allowing CBT to be converted into a short, structured format. Thus, CBT will be the basis for supportive feedback (daily health tips) in the intervention.

*Coping skills training*: as part of CBT-based practices, coping skills training refer to a persons’ perceived ability to effectively cope with adversity and distress, by using adaptive (constructive) coping strategies in stressful situations or during conflicts. Developing active, good coping skills is associated with improved mental health including depression (77), anxiety (78), and psychological distress (79). Improvements in coping skills are also associated with less engagement in avoidance behavior toward potentially anxiety-inducing situations, which in turn leads to increased participation in social activities as a protective factor for the maintenance of mental health (80).

*Behavioral activation*: aiming toward breaking the “vicious cycle” of low mood and inactivity, behavioral activation is a CBT-technique that encourages the user to engage in physically activating and rewarding activities, e.g., by planning of activities, setting goals, and engaging in pleasurable activities. Behavioral activation is associated with improvements in depression (81) and anxiety (82). As part of the daily health tips, we will select short, tangible, and universal activities to maximize user engagement with behavioral activation. By encouraging reflection on the experience after performing an activity, the tips will stimulate reflective learning.

###### Design

To facilitate the adoption and ease of use of the intervention, the smartphone application will be designed toward usability (user-centered design) (83, 84). For example, a tutorial will explain the features and navigation upon initial start of the application. Based on process evaluations, four usability themes for the development of smartphone applications will be considered: design, feedback, navigation, and terminology (85). Design refers to the applications’ interface layout, taking into account consistency, location of icons, and functions on each screen (e.g., the size, color, and esthetics of visual elements). Feedback refers to the applications’ ability to provide appropriate feedback, aimed toward assisting and guiding the user during completion of tasks (e.g., indicating sync status by color when submitting self-monitoring data). Navigation refers to optimizing the way a user navigates throughout the application, so that users know where they are in the application at all times and how to get back to where they came from (e.g., clear icons, tab views, and buttons). Terminology means that the user is able to identify and understand the language used within the application (e.g., avoidance of technical terms).

#### Control Groups

The intervention will be compared to two control groups: first, the active control group will complete daily AAs (self-monitoring without support). Second, there will be a passive control group (no self-monitoring and no intervention).

#### Pilot Test

Prior to recruitment, a pilot test of will be conducted among a sample of 30 students at Charité Universitätsmedizin Berlin, who will receive either course credit or 20€ compensation. All study procedures will be pilot tested.

#### Participant Incentives

To enhance adherence with the study protocol, participants who complete all outcome assessments will receive an incentive of 25€.

Potential “gaming” needs to be avoided, which refers to a situation where research participants fraudulently enroll in a study for the purpose of acquiring research payment. A first measure to prevent gaming is that the eligibility survey will be locked in case of participants trying to change submitted answers. A second measure is that study links will only be available for one user/device. Third, IP addresses will be tracked to prevent duplicate enrollment.

#### Data Storage and Privacy

All data will be stored and handled to fulfill the legal requirements of German data protection. Data is stored in a data center in Greifswald, Germany, which is operated by a German hosting provider (“ProfitBricks GmbH”) certified according to ISO 27001 and Trusted Cloud. To prevent that the identity of the subjects is stored on the server, no person-related data will be collected together with the self-monitoring data (e.g., name). Additionally, a numerical pseudonym label will be assigned, the so-called participant identifier. Participants’ study data can only be linked with person-related data by using the participant identifier. After data collection the participant identifier will be deleted. All communication between smartphone and the server, as well as communication between server and researcher will be encrypted with a 256 Bit Secure Sockets Layer encryption. Finally, to ensure that no unauthorized parties can access the participant data, e.g., in the case of losing the device, all data stored locally on the smartphone will be encrypted with Advanced Encryption Standard 256 bit technology. Each time the participant uses the application, a unique session key is generated to encrypt and securely transmit the data to the server. Only with the private key stored on the server the data can be decrypted. After data transmission from the device to the server, local data stored on the device is deleted.

#### Additional Procedures

*Telephone reminders*: to limit study drop-out, telephone reminders will be initiated in the case of failure to respond to an outcome assessment or failure to download the smartphone application. The study team will constantly supervise enrollment, downloads of application, and compliance with the study protocol, and will initiate telephone calls to participants that need to be reminded.

*Application reminders*: to increase adherence and to stimulate user engagement with the intervention, push notifications on the Android device will remind participants to complete the daily self-monitoring report and will remind users to engage with intervention content, e.g., by displaying a notification that a new daily health tip is available.

### Outcomes

Study outcomes are assessed at four time points: screening (T0), baseline (T1), post-assessment (T3) and follow-up (T4). While the screening (T0) relies on self-assessments collected during participant registration on the study website, structured telephone interviews are conducted at T1, T2, and T3 to assess the primary outcome. The telephone interviews will be conducted by the Academic Survey Lab at the University of Hamburg. Trained interviewers who are blinded to the study condition will conduct the interviews, resulting in an independent outcome assessment to avoid confounding with the self-monitoring data. The secondary outcomes will be self-assessed on the smartphone for all three groups.

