## Abstract

Mobile health (mHealth) could be widely used in the population to improve access to psychological treatment. In this paper, we describe the development of a mHealth intervention on the basis of supportive self-monitoring and describe the protocol for a randomized controlled trial to evaluate its effectiveness among smartphone users with psychological distress. Based on power analysis, a representative quota sample of *N* = 186 smartphone users will be recruited, with an over-sampling of persons with moderate to high distress. Over a 4-week period, the intervention will be compared to a self-monitoring without intervention group and a passive control group. Telephone interviews will be conducted at baseline, post-intervention (4 weeks), and 12-week follow-up to assess study outcomes. The primary outcome will be improvement of mental health. Secondary outcomes will include well-being, intentions toward help-seeking and help-seeking behavior, user activation, attitudes toward mental-health services, perceived stigmatization, smartphone app quality, user satisfaction, engagement, and adherence with the intervention. Additionally, data from the user’s daily life as collected during self-monitoring will be used to investigate risk and protective factors of mental health in real-world settings. Therefore, this study will allow us to demonstrate the effectiveness of a smartphone application as a widely accessible and low-cost intervention to improve mental health on a population level. It also allows to identify new assessment approaches in the field of psychiatric epidemiology.

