#### Sample Size Calculation

A power analysis was performed to detect a group difference on the primary outcome at post-assessment group. The calculation is based on the assumption that a difference between the supported monitoring group and either AA group or control group within the margin −0.25 < Cohen’s *d* < 0.25 can be neglected. We assume no difference between the two latter groups. Therefore, a between-group difference of *d* = 0.25 should reach statistical significance as an indicator of the general effectiveness of the intervention. The target sample size was computed using Gpower (40) for a repeated-measures analysis of variance for a within-between interaction of time and group (ANOVA). We used a targeted power of 95%, a significance level alpha of 0.05, four assessment waves, a conservative estimate of correlation between measurements (*r* = 65) and variances of the differences between groups (non-sphericity correction epsilon = 0.8). This results in a total *N* = 141. Adding 20% drop-out at T2 and T3, we will include 186 participants (62 per group).

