### Statistical Analysis

Before analysis, data will be prepared and cleaned according to the guidance in Ref. (99). Data will then be analyzed according to the recommendations in the CONSORT statement for evaluation of e-health interventions, as well as the mHealth evidence reporting and assessment checklist from the WHO mHealth Technical Evidence Review Group (100, 101). Intention-to-treat analysis (ITT) and additional per-protocol analysis (PP) will be performed, the former including the data of all participants randomized and the latter using only the subset of participants who complete all assessments (T0, T1, T2, T3).

Multilevel models are an appropriate data-analytic strategy for smartphone data, involving daily measurements, resulting in repeated observations nested within individuals (102). These models are well suited to test the general effectiveness of supported monitoring among smartphone users, but also its differential effectiveness and its conditional effectiveness. Models include analysis of both within-person and between-person variance. Missing data will be replaced using Markov Chain Monte Carlo multiple imputation, which is considered to produce more precise estimates of the true intervention in the ITT analysis compared other imputation methods, i.e., last observation carried forward (103).

*General effectiveness*: to test for changes in the outcome variable from before to after the intervention period, repeated-measures analysis of variance (RM-ANOVA) will be conducted for each intervention outcome (104). In the RM-ANOVA, the within-person effect of time is used as an index of general intervention effectiveness. For the analysis of between-person variance, the model can be extended to multivariate analysis of variance (MANOVA). In this case, a between-subjects factor for group membership is added (Supported monitoring group vs. AA group vs. control group). If there is an interaction between the time factor and the group factor, we will conclude that the intervention was effective.

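### The online screening score (T0) is counted as one of four repeated-measures waves, so a change of mode can enter the time effect and the stated N of 141 rests on a pre-treatment wave

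*Protocol article*

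**What the plan says.** Under Outcomes, the article states: "Study outcomes are assessed at four time points: screening (T0), baseline (T1), post-assessment (T3) and follow-up (T4"). It then splits the modes: "the screening (T0) relies on self-assessments collected during participant registration on the study website, structured telephone interviews are conducted at T1, T2, and T3", and it is the interviews that are meant to assess the primary outcome. The Abstract agrees that there are three interviews: "Telephone interviews will be conducted at baseline, post-intervention (4 weeks), and 12-week follow-up to assess study outcomes".

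The primary outcome is the K6. Target Group defines the distress groups by the K6, and Sample Description says that users are pre-screened on distress. The K6 is therefore taken online at T0. This is inferred from several sections, since no single sentence says it.

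Sample Size Calculation assumes "four assessment waves" for the time by group interaction of a repeated-measures ANOVA. Statistical Analysis says that "the within-person effect of time is used as an index of general intervention effectiveness" and that effectiveness will be concluded if time and group interact. It limits the per-protocol set to "participants who complete all assessments (T0, T1, T2, T3"). No text adjusts for mode, argues that the two modes are equivalent, or restricts the model to the interviews.

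**The concern.** Two features set T0 apart from the other waves. It is self-completed on a website, while the rest are asked by an interviewer. It also precedes the intervention, so the step from T0 to T1 cannot carry a treatment effect. If participants report more or less distress to an interviewer than online, that step moves in every arm with no change in mental health, and the within-person time effect registers it. A reader who takes that effect as the index of effectiveness, as the plan invites, could credit the app with a change of questionnaire mode.

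The second consequence is for the sample size. In the formula used, each added wave raises the noncentrality, so a wave that cannot respond to treatment lowers the required N.

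**Working it through.** **1. Which wave is the fourth?** The interviews fall at baseline, 4 weeks and 12 weeks, which makes three. The power analysis uses four. The only other listed time point is T0.

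**2. Reproducing N = 141.** Inputs from Sample Size Calculation: d = 0.25, so f = d/2 = 0.125; alpha 0.05; power 95%; r = 0.65 (printed without its decimal point); epsilon = 0.8. There are k = 3 groups. For the G*Power within-between interaction with m waves:

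- noncentrality λ = N·m·f²·ε/(1 − r)
- df1 = (k − 1)(m − 1)ε
- df2 = (N − k)(m − 1)ε

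| Waves m | N | λ | df1, df2 | Power |
|---|---|---|---|---|
| 4 | 140 | 20.00 | 4.8, 328.8 | 95.1% |
| 4 | 141 | 20.14 | 4.8, 331.2 | 95.3% |
| 3 | 141 | 15.11 | 3.2, 220.8 | 90.8% |
| 3 | 149 | 15.96 | 3.2, 233.6 | 92.4% |
| 3 | 166 | 17.79 | 3.2, 260.8 | 95.0% |
| 3 | 168 | 18.00 | 3.2, 264.0 | 95.3% |

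Four waves give 140, or 141 in equal groups, which is the stated figure. Three waves with every other stated input unchanged give 166, or 168 in equal groups. The 149 is 186 × 0.8 = 148.8, rounded.

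**3. Effect of a mode shift on the time effect.** Assume unit SD, r = 0.65 between all waves, no true change, and a shift s at T0 that is equal in all arms. Then λ = N·s²·(m − 1)/m/(1 − r) = 186 × s² × 0.75/0.35, with 3 and (186 − 3) × 3 = 549 degrees of freedom and a critical F of 2.62.

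- s = 0.1: λ = 3.99, time effect significant in about 35% of trials
- s = 0.2: λ = 15.94, about 93%

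A simulation of 4,000 trials per setting (62 per arm) gave 36% and 93%, against about 5% with no shift. In the same simulation the time by group interaction stayed between 4.6% and 5.6% for every assumed shift from 0 to 0.5 SD.

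**4. What a T0 covariate recovers.** Take the supported arm against the pooled controls, on the mean of the two post-baseline interviews, with d = 0.25 and 20% dropout (50 against 99). The variance of that mean is (1 + 0.65)/2 = 0.825.

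- Adjusted for T1 only: 0.825 − 0.65² = 0.4025; SE = √[0.4025(1/50 + 1/99)] = 0.110; power about 0.62.
- Adjusted for T1 and T0, with T0 correlating 0.65 with the interviews: 0.825 − 2(0.4225)/1.65 = 0.313; SE 0.097; power about 0.73.
- The same with T0 correlating only 0.5: 0.825 − (0.4225 + 0.25 − 0.325)/0.75 = 0.362; SE 0.104; power about 0.67.

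This contrast is not the interaction test that the plan powers. It shows only how the gain depends on the correlation between modes.

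**The case against.** The strongest objection is that the decision rule is untouched. The plan concludes effectiveness from the time by group interaction and powers that test. Randomisation makes a mode shift common to the arms, and a common shift cancels from the interaction. This stands. A reader might infer from the 35% and 93% that the trial would falsely declare the app effective that often. The documents do not support that, because those rates belong to the overall time effect alone.

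A second objection is that Statistical Analysis never lists the waves in the ANOVA. T0 appears there only in the definition of completers, so that list does not prove that T0 is an outcome wave. This also stands. The reading rests on the four time points under Outcomes, the four waves in the power analysis and the exact match at 141. Other text points towards three waves: the interviews are what assess the primary outcome, and Cohen's d already takes its SD from the baseline assessment, which the article labels T1. The article is thus inconsistent, rather than clearly committed to a mixed-mode outcome.

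Third, no passage gives a mode difference for the K6, or its direction, or shows that one exists. The percentages are conditional on assumed shifts. Rejection rates for a single arm could be calculated too, but the plan states no within-arm test to attach them to.

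Finally, the time effect is a weak index in any case, because it is uncontrolled. Natural course, repeated questioning, or regression to the mean after selection on T0 could move it too. Dropping T0 removes the mode component but does not make a within-person change a randomised comparison. This is a reason to rest the conclusion on the interaction as well.

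**Conclusion.** The point holds in a limited form. Outcomes and Sample Size Calculation count a pre-treatment online self-report as a repeated-measures wave alongside three telephone interviews. Two consequences follow.

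- The within-person time effect, named as an effectiveness index, is open to a mode difference of unknown size. The figures of about 35% and 93% assume shifts of 0.1 and 0.2 SD, equal correlations of 0.65, N = 186 and no true change.
- N = 141 delivers 95% power only with T0 counted. On three waves power is 90.8% at 141 and 92.4% at 149, on the plan's own effect size, correlation and epsilon.

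The randomised comparison is not biased by a shift common to all arms. Nor does the higher three-wave N mean that the planned 186 is inadequate: at 149 completers the shortfall from the 95% target is under three percentage points.

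**What to change.** - In Statistical Analysis, state that the K6 outcome consists of the three telephone interviews (baseline, post-assessment, follow-up) and that change and the Reliable Change Index are measured from T1.
- Use the T0 K6 as a baseline covariate, not as an outcome wave.
- Rest the effectiveness conclusion on the time by group interaction and stop naming the within-person time effect as the index.
- In Outcomes, describe T0 as screening only and reconcile the visit labels: post-assessment and follow-up are T3 and T4 in one sentence, while the next places the interviews at T1, T2 and T3.
- In Sample Size Calculation, restate the power for three waves: about 92% at 149 completers.

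The cost goes a little beyond analysis wording, because the stated power becomes slightly less favourable. Enrolment can stay at 186. How much the T0 covariate recovers depends on its correlation with the telephone scores, which the documents do not give, so the recovery should not be promised in advance.
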